### Study population

A birth registry has been developed, which leverages the biannual update of the HDSS by cross-tabulation of expected birthdates in the selected kebeles based on the date of the mother’s last menstrual period and the estimated month of pregnancy at the time of the interview. Data on expected deliveries were updated every month, and one DHSS data collector was assigned per kebele to record actual births. Newborn children were randomly selected with the aim to include 12 infants per kebele in the first month after birth. Families were eligible for participation if they had no plans to move out of the Haramaya woreda within 6 months; the mother had resided in the woreda for at least 3 months during pregnancy; and the mother was over 16 years of age when giving birth. Infants were excluded if the birth weight was <2500 g, if the infant or mother required extended stay (more than 4 days) in the hospital after birth, or if the infant had visible congenital abnormality or known serious medical illness or enteropathy, diagnosed by a medical doctor. Enrolment started in December 2020 and was completed by June 2021; 115 infants have successfully been enrolled (table 1). Written informed consent was obtained from all participating households (husband and wife) using a form in the local language (Afan Oromo).

### Infant health measurements and interviews

Infants are followed up from birth to 1 year of age. At enrolment and every 3 months anthropometric measurements (age in days, recumbent length, weight, mid-upper arm circumference (after 6 months of age) and head circumference) are collected.

At the end of the follow-up period (age 12–14 months), EED is detected by a combination of the lactulose absorption test^31^ and analysis for faecal myeloperoxidase (MPO) using a commercially available ELISA MPO RUO assay (Alpco, Salem, New Hampshire, USA).

### Collection and management of biological samples

Stool samples are obtained every 4 weeks from all infants and biannually from all mothers, siblings and livestock (one sample from chickens, cattle, goats and sheep per household). Samples from the environment (three soil samples using bootsocks and one sample of drinking water per household) are also collected biannually.

Mothers are provided modified disposable diapers with a clean plastic sheet, sterilised by UV for 10 min and an ice box with ice pack on the day before sample collection. The mother is asked to fit the modified diaper to the infant in the early morning and, after the infant has defecated, to wrap and place the diaper and contents in the ice box. When appropriate, the mother collects a sample of stool from the youngest sibling, as above, and of her own stool in a screw cap bottle. Stool samples are transferred to sterile prelabelled whirl-pack bags, which are transported to the lab in ice boxes.

Samples are transported to a dedicated laboratory at the HU main campus (figure 1) in an ice box within a maximum of 6 hours. Samples for nucleic acid extraction and sequencing are transferred to a nucleic acid stabilising reagent. On arrival in the laboratory, remaining faecal samples are distributed over barcoded tubes and frozen at – 80°C, partly with addition of 15% v/v glycerol. Samples for MPO analysis are distributed in barcoded tubes in the field, immediately flash-frozen in liquid nitrogen and stored at – 80°C immediately on arrival in the laboratory.

### Data collection and management

All data are collected by trained personnel employed by HU who are proficient in the local language (Afan Oromo), knowledgeable of the local cultural background, and have appropriate scientific backgrounds (health sciences, veterinary sciences and social sciences).

Household questionnaires on demographics; livelihoods; wealth; animal ownership, management and disease; WaSH; infant health and nutrition; and women’s empowerment are presented to mothers and fathers two times during the study. Mothers answer a short questionnaire on infant health, vaccinations, breastfeeding practices, antibiotic use and diets during monthly collection of the stool samples. Families who decide to discontinue participation are presented with an exit interview. All data are collected on tablets using the REDCap mobile app and uploaded to a REDCap database, hosted at the University of Florida. The REDCap codebook is available as online supplemental file 1.

10.1136/bmjopen-2022-061311.supp1Supplementary data

### Detection, quantification, isolation and characterisation of *Campylobacter* spp in human stools, livestock faeces and environmental samples

#### Molecular detection of *Campylobacter* spp

Genomic DNA is extracted from the field samples using commercial kits. Detection and quantification of *Campylobacter* is performed using genus-specific Taqman real-time PCR^32^ and species-specific Sybr Green real-time PCR.^32–36^ Stool samples with a Ct value lower than 35 and 1 Ct value below the negative controls (sterile water, *Salmonella enterica* ssp *enterica* serotype Typhimurium strain LT2 and *Escherichia coli* genomic DNA) are considered positive for *Campylobacter*.

#### Detection of *Campylobacter* spp. by culture

Samples positive for *Campylobacter* by qPCR and a random selection of 10% of negative samples are selected for detection of thermophilic and non-thermophilic *Campylobacter* spp. For thermophilic *Campylobacter* spp, decimal dilutions are plated on CHROMagar *Campylobacter* (DRG International, Springfield, New Jersey USA) and incubated for up to 48 hours at 42°C in microaerophilic conditions (85% nitrogen, 10% carbon dioxide, 5% oxygen) using anaerobic jars and GasPak EZ Campy Container System Sachets. For non-thermophilic *Campylobacter* spp, decimal dilutions are plated on Columbia agar supplemented with 5% defibrinated sheep blood, Skirrow supplement (2 µL/mL), amphotericin B (5 µg/mL), cefoperazone (8 µg/mL) and *Campylobacter* growth supplement. The plates are incubated at 37°C for up to 72 hours in anaerobic conditions using anaerobic jars and GasPak anaerobic sachets. If no characteristic growth is observed, samples are enriched in Preston broth (faeces, soil samples for thermophilic *Campylobacter* spp) or Bolton broth (otherwise), incubated and plated as above.

A random selection of up to five presumptively positive colonies from each sample and assay are confirmed by real-time PCR using genus-specific primers.^37^ Colonies confirmed as *Campylobacter* spp. are stored in glycerol at −80°C and shipped to the US for speciation using matrix-assisted laser desorption/ionization time-of-flight (MALDI-TOF) mass spectrometry and whole-genome sequence analysis of confirmed isolates.

#### Metagenomic sequencing

Metagenomic sequencing will be used to complement detection and genetic characterisation of *Campylobacter* sp in children, mothers, siblings and livestock by with a culture-independent method providing sequences of (genes from) the dominant *Campylobacter* sp. These data will also serve to validate qPCR results and are expected to provide information on infection with other enteric pathogens. We aim to apply 16s rRNA sequencing^38^ to infant stool samples after birth and at 4, and 12 months as well as at the time of EED measurement, and to all available stool samples from siblings and mothers. Shotgun sequencing^24^ will be applied to a random selection of DNA extracts from human and livestock samples from 45 households.

### Data analysis

#### Objective 1

The prevalence, species composition and genomic diversity of thermotolerant and non-thermotolerant *Campylobacter* spp. in infants, adults, livestock and other reservoirs in the Haramaya woreda will be characterised by descriptive analysis; identification of species and clonal complexes using legacy, core genome and/or whole-genome MLST: phylogenetic analysis,^39^ determination of index of diversity, linkage equilibrium and rarefaction analysis.^40^ Further, the virulome and resistome of the *Campylobacter* isolates will be analysed using comprehensive virulence factors^41^ and antibiotic resistance gene databases.^42^ In addition, a functional profiling of the sequenced genome will be predicted.^43^ Specificity and sensitivity of qPCR and culture methods for detecting *Campylobacter* at the genus and biological group levels will be evaluated using Bayesian modelling of performance characteristics in the absence of a gold standard.^44–46^ Metagenomic sequencing data will be analysed by analysed by latest versions of QIIME V.2,^47^ CCMetagen^48^ and IDseq pipelines.^49^

We will fit a Bayesian two-state Markov model for the temporal process of colonisation and clearance of *Campylobacter* in each infant. The daily transition probabilities between colonisation and clearance will be regressed on time, demographic variables, household characteristics and most recent *Campylobacter* prevalence among samples from livestock, environment and other household members (sampled biannually).

Spatiotemporal effects will be analysed using boosted regression trees^50^ to model the influence of regional environmental variables on the distribution of infections of infants with the *Campylobacter* genus as primary outcome variable. Depending on results, this analysis will also be performed for one or more dominant species. To explore the spatial heterogeneity of effects of covariates on *Campylobacter* infections geographically weighted logistic regression models^51^ will be used.

#### Objective 2

The primary outcome variable for this objective is the proportion of *Campylobacter* infections in infants to that is attributed to mothers, siblings, livestock and environmental reservoirs based on the genetic population structure of *Campylobacter* sp circulating in these reservoirs. Source attribution will be based on modified Hald^52^ and asymmetric island^53^ models using R packages sourceR^54^ and islandR (https://github.com/jmarshallnz/islandR). We will also explore the use of whole-genome^55 56^ and metagenomic sequencing data^57^ for attribution.

#### Objective 3

Data on sociodemographics, livelihoods, economics, environmental health and sanitation will be analysed descriptively, characterising the context within which the study is occurring. Infant health, including breastfeeding practices, infant diet, vaccination status, use of antibiotics and presence of fever and diarrhoea, will also be described. Women’s empowerment in agriculture will be assessed using five domains of empowerment generated by the Women’s Empowerment in Agriculture Index (WEAI). Within this context, the primary outcome variables (EED biomarkers and nutritional outcome data, including length-for-age Z score and stunting status) will be examined for their associations with the cumulative burden of *Campylobacter* using generalised linear models and generalised estimating equations, respectively. We will adjust for potential confounders including sex, socioeconomic status and kebele residence, and include potential covariates such as breast feeding, infant health, household WaSH conditions, animal ownership, WEAI and food security. To better estimate the cumulative burden of *Campylobacter* we will extract data from the Bayesian Markov model that simulates the underlying daily presence/absence status of any *Campylobacter* sp in symptomatic or asymptomatic children. We will also perform exploratory analysis of associations between the gut microbiome of infants and infection with *Campylobacter* spp, EED biomarkers and stunting.

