## Methods and analysis

### Study setting

The study is conducted in the rural Haramaya woreda, East Hararghe zone, Oromia Region, Ethiopia (figure 1). Haramaya woreda, at an altitude of 1400–2340 m above sea level, has 36 rural kebeles (the smallest administrative unit in Ethiopia) and three urban kebeles. Khat, vegetables and fruits are important cash crops.

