**Figure 1 F1:**
[figure not shown]
Geographic location of study area. Right panels from top to bottom: Ethiopia, East Hararghe zone, Oromiya region with Haramaya woreda indicated in purple. Left panel: Haramaya woreda with study sites indicated in purple. Haramaya University (HU) campus is indicated in orange. The urban centre of Harar borders the woreda to the East. AM, Amuma; AW, Adele Walta; BG, Biftu Geda; BK, Bachake; DA, Damota; GC, Gobe Challa; IO, Ifa Oromia; KR, Kuro; NG, Nageya; QD, Qerensa Dereba.

According to the 2016 Ethiopian Demographic and Health Survey, stunting in Haramaya is higher at 45.8% than the national average of 38%.^28^ Haramaya University (HU) has established a Health and Demographic Surveillance Site (HDSS) in 12 kebeles in the Haramaya woreda.^29^ Overall, 10 of these 12 kebeles (figure 1) will provide the source population for the study. Two kebeles were excluded because of small population size and proximity to the urban centre of Harar. The total population of the 10 kebeles is 92 900, with population numbers per kebele ranging between 4900 and 14 300 (table 1).

**Table 1 T1:** Population size and number of participating households in selected kebeles

Kebele	Population	Participants	Kebele	Population	Participants
Adele Walta (AW)	5100	11	Gobe Challa (GC)	14 300	12
Amuma (AM)	7400	12	Ifa Oromia (IO)	12 200	11
Bachake (BK)	4900	9	Kuro (KR)	11 700	12
Biftu Geda (BG)	11 700	12	Nageya (NG)	11 500	12
Damota (DA)	6600	12	Qerensa Dereba (QD)	7500	12

Source: Haramaya University Health and Demographic Surveillance Site (unpublished).

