### Sample size and power

The study is powered for prevalence estimation. A sample of 100 infants or animals allows estimation of a 50% prevalence with precision 10% at 95% confidence, and a power of 80%. We allowed for 20% attrition and aimed to enrol a sample of 120 newborn infants.

Overall, 100 pure cultures of each thermotolerant and non-thermotolerant *Campylobacter* spp. per reservoir (infants, mothers, siblings, four livestock species (cattle, goat, sheep, chicken), water, soil) are analysed by whole-genome sequencing, 1400 in total. This power calculation is based on Smid *et al*,^30^ who showed that the precision of attribution is reduced if less than 100 isolates per animal reservoir are used.

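### The stated ±10-point prevalence precision fits, at best, the ten study kebeles, not the Haramaya woreda that Objective 1 names

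*Protocol article*

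**What the plan says.** The Protocol article's *Sample size and power* section bases the sample size on how precisely a prevalence can be estimated: "A sample of 100 infants or animals allows estimation of a 50% prevalence with precision 10% at 95% confidence". It mentions no design effect, ICC or kebele clustering.

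The list of objectives in the Introduction and the *Data analysis* section (Objective 1) both place the prevalence in the Haramaya woreda. *Data analysis* adds only that it "in infants, adults, livestock and other reservoirs in the Haramaya woreda will be characterised by descriptive analysis". It names no interval formula and no weighting.

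*Study setting* says that the woreda "has 36 rural kebeles (the smallest administrative unit in Ethiopia) and three urban kebeles". The text below Figure 1 says that "10 of these 12 kebeles (figure 1) will provide the source population for the study". These are the kebeles of a surveillance site, less two that were excluded for small population size and closeness to the urban centre of Harar. *Study population* says: "Newborn children were randomly selected with the aim to include 12 infants per kebele". Table 1 shows 9 to 12 participants per kebele, 115 in total, from kebele populations of 4900 to 14 300 (total 92 900).

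**The concern.** The precision and the target belong to different populations. Within the ten kebeles, infants were drawn at random in every kebele. The kebeles are then strata, and differences between them add no sampling error. For the whole woreda the ten kebeles are a subset of the units, and differences between kebeles become a source of error that the 10-point figure leaves out.

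The protocol itself expects geography to matter. Objective 1 plans to model regional environmental variables and spatial heterogeneity in infant infection, and Objective 3 adjusts for kebele of residence. The headline precision nevertheless assumes no kebele variation at all.

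Prevalence is the quantity on which the study is sized. If a woreda prevalence were published with the planned precision, it would look more certain than the design allows. The limitations in the Discussion mention the small sample for nutritional associations, but neither the kebele sampling nor the non-random choice of kebeles.

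**Working it through.** **Inputs from the protocol.** Prevalence p = 0.50, half-width d = 0.10, 95% confidence, n = 100 (*Sample size and power*). Enrolled: 115 in 10 kebeles, with sizes and populations from Table 1. Rural kebeles in the woreda: 36 (*Study setting*).

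**Assumed.** No ICC is given, so I use 0.02, 0.05 and 0.10.

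**1. Reproduce the plan's figure.** n = 1.96² × 0.25 / 0.10² = 96.04, so 97, close to the stated 100. At n = 100 the half-width is 1.96 × √(0.25/100) = 9.8 points; at n = 115 it is 9.1. The 10-point figure is therefore the simple-random-sample result.

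**2. Woreda target, kebeles treated as if drawn at random.** Design effect = 1 + (m − 1) × ICC, with m = 10 at n = 100 and m = Σnᵢ²/Σnᵢ = 11.57 at n = 115. Half-width = 1.96 × √(0.25 × design effect / n). Allowing for 10 of 36 kebeles sampled, the variance at n = 100 is 0.25 × [ICC × (1 − 10/36)/10 + (1 − ICC)/100].

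| Assumed ICC | Design effect (n = 100) | Half-width, n = 100 | Same, with 10-of-36 factor | Half-width, n = 115 |
|---|---|---|---|---|
| 0.02 | 1.18 | 10.6 | 10.4 | 10.1 |
| 0.05 | 1.45 | 11.8 | 11.2 | 11.3 |
| 0.10 | 1.90 | 13.5 | 12.5 | 13.1 |

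Without the 10-of-36 factor, the half-width passes 10 points once the ICC exceeds about 0.005 at n = 100, or about 0.019 at n = 115.

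**3. Coverage of a simple-random-sample interval for the woreda.** Simulation of 20,000 draws: 36 kebeles with beta-distributed prevalence, 10 sampled at random, 10 infants in each. Coverage of the nominal 95% interval is about 93%, 91% and 87% at ICC 0.02, 0.05 and 0.10. The formula without the finite-population factor, 2Φ(1.96/√design effect) − 1, gives 92.9%, 89.6% and 84.5%.

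**4. Ten-kebele target, kebeles as strata.** Between-kebele variation does not widen the interval. Near-equal numbers from unequal populations do call for weights wₕ = Nₕ/nₕ. The Kish factor is n × Σ(Nₕ²/nₕ) / (ΣNₕ)² = 115 × 82,320,731 / 92,900² = 1.097. Half-widths: 9.80 × √1.097 = 10.3 points at n = 100 and 9.14 × √1.097 = 9.6 at n = 115. This takes total population as a stand-in for births, which are not given by kebele, and the Table 1 allocation for both sample sizes.

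**The case against.** **The protocol defines its population.** It calls the ten kebeles the source population, and the abstract says that infants are selected from ten kebeles. The mention of the woreda may only give a location. This has force, and on that reading the stated precision nearly applies. But Objective 1 as worded names the woreda, in two places, and nothing in *Sample size and power* limits the precision to the ten kebeles.

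**The planned intervals are not known to be too narrow.** A reader might infer that the analysis itself will give under-covering intervals. The documents do not support that. *Data analysis* says only that the analysis is descriptive, and an interval method may stand in an analysis plan that is not shown. What can be criticised is the stated planning precision set against the stated target.

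**The size depends on an assumed ICC.** True. At ICC 0 there is no loss, and with all 115 infants retained the half-width stays within 10 points up to an ICC of about 0.019.

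**A wider cluster interval would not rescue the woreda figure.** One could compute the interval from kebele-level results with 9 degrees of freedom. Simulated half-widths are then 12.0, 13.3 and 15.3 points at the three ICCs. A reader might take ±12 to 15 points as the correct woreda precision. It is not. The kebeles were not a random draw, so no such interval is valid for the woreda. Part of that widening is also the penalty for few degrees of freedom: at ICC 0 the same interval is already about 11.0 points (2.262 × 5.0 × 0.973), some 1.2 more than 9.8.

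**Urban kebeles.** Counting the three urban kebeles as missing is doubtful, because *Study setting* describes a rural study. The point rests on the 26 rural kebeles.

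**Conclusion.** The point holds as a mismatch between target and precision. The 10-point figure is exact for a simple random sample and roughly right for the ten kebeles as weighted strata. It is not a precision for the woreda.

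The sizes for the woreda are illustrative. They assume an ICC of 0.02 to 0.10 and a random choice of kebeles that did not happen. They show overstatement of modest to moderate size. Non-random selection is the larger problem, and no interval width repairs it. The point should be corrected, but it does not threaten the data or the other objectives.

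**What to change.** 1. In Objective 1, both in the Introduction and in *Data analysis*, name the ten study kebeles instead of the Haramaya woreda as the population for prevalence.
2. Compute the prevalence interval with kebele as stratum and weights for kebele population.
3. In *Sample size and power*, state that the precision refers to those ten kebeles, and give it as about ±10.3 points at n = 100 or ±9.6 at n = 115.
4. Describe any extension to the woreda as a generalisation limited by the non-random choice of kebeles. List this among the limitations, and attach no design-based interval to it.

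Data collection does not change. The cost is a few words and a standard survey-type interval. The downside is a narrower claim and, at n = 100, a slightly wider stated precision.

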We conducted a cross-sectional study of smallholder farming households in Haramaya woreda (district) in rural eastern Ethiopia to measure the prevalence of *Campylobacter* spp., EED and undernutrition in children aged 10–16 months old and related risk factors.^23^ A combination of poor child diet, inadequate WaSH conditions and poor livestock waste management potentially accounted for a high prevalence of (predominantly asymptomatic) *Campylobacter* spp colonisation, EED and undernutrition. Although the study was powered for prevalence estimation, current breastfeeding status of the child and child consumption of ASF were both significantly associated with *Campylobacter* spp. colonisation, while access to improved drinking water was protective against EED. Notably, we found a diversity of *Campylobacter* spp. colonised the children’s gut, with non-thermotolerant species occurring more frequently and in higher abundance than thermotolerant species.^24^ Although previous studies investigated the health impact and reservoirs of non-thermotolerant species, none of them targeted low-income and middle-income country settings and CU5 as study population.^25–27^ The findings from our cross-sectional study underscore the need for attribution research examining various livestock species and other potential reservoirs for *Campylobacter* colonisation of infants. This paper presents a longitudinal study protocol and adaptations that have been implemented due to political unrest and the COVID-19 pandemic.

The objectives of the longitudinal study are:

To assess the prevalence, species composition, and genomic diversity of thermotolerant and non-thermotolerant *Campylobacter* spp. in infants, adults, livestock and other reservoirs in the Haramaya woreda.To determine the attribution of *Campylobacter* infections in infants to humans, livestock and other reservoirs (ie, drinking water, soil) based on the genetic population structure of *Campylobacter* spp. circulating in these reservoirs.To assess the associations among the presence of *Campylobacter* spp. and the nutritional status (i.e., stunting) of infants in relation to their socioeconomic environment.

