We follow the current standard of care in Ethiopia for the management of sick children. Accordingly, treatment will not be provided for asymptomatic *Campylobacter* infections. All infants with acute disease (diarrhoea, fever) or severe acute malnutrition are linked with the nearby health facility. Transportation to the facility and referral arrangements are offered by the project.

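### The colonisation and clearance model does not name the antibiotic use and breastfeeding recorded with each stool, so its clearance rate mixes treated and untreated clearance

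*Protocol article*

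**What the plan says.** Data analysis, Objective 1, states: "We will fit a Bayesian two-state Markov model for the temporal process of colonisation and clearance of" the genus in each infant. The transition probabilities "will be regressed on time, demographic variables, household characteristics and most recent" prevalence in other reservoirs, described as "prevalence among samples from livestock, environment and other household members (sampled biannually". Apart from time, this is the only regressor described as being updated during follow-up, and it changes twice a year.

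The infants are observed far more often. Collection and management of biological samples says: "Stool samples are obtained every 4 weeks from all infants". Data collection and management adds: "Mothers answer a short questionnaire on infant health, vaccinations, breastfeeding practices, antibiotic use and diets during monthly collection of the stool samples".

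Objective 3 takes its cumulative burden from the simulated daily status in this same Markov model. It also says that infant health, including "use of antibiotics and presence of fever and diarrhoea, will also be described". It lists breastfeeding and infant health among the possible covariates of the growth and enteric dysfunction models. The Introduction reports from the team's cross-sectional study that "current breastfeeding status of the child and child consumption of ASF were both significantly associated with" colonisation.

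**The concern.** Antibiotic use is an infant-level factor that changes over time and can act directly on one of the two transitions being modelled. If it is left out, the fitted clearance rate is an average over treated and untreated time. A reader who takes it as the natural course of carriage would think untreated colonisation shorter than it is. Breastfeeding changes during the first year and was associated with colonisation in the team's own data. Without it, the livestock and environment effects on acquisition are estimated with a known candidate predictor missing.

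The model also supplies the Objective 3 exposure. A single clearance rate is too low on treated days and too high on untreated days. Reconstructed days between samples may therefore be too many in treated infants and too few in untreated infants. If treated infants are also the sicker ones with poorer growth, which is plausible but not documented, the error would be related to the outcome.

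**Working it through.** **1. The text.** The Objective 1 sentence lists its regressors without an opening such as *including* or *for example*. The Objective 3 covariate sentence does use open wording. Antibiotic use, breastfeeding and diet are not normally classed as demographic or household variables. All three are available at each 4-weekly stool.

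**2. Clearance rate.** The documents give no antibiotic frequency, antibiotic effect or carriage duration, so all three are assumed here. Let λ be the natural daily clearance rate, p the share of 28-day intervals with a course, and e the share of carriers whom a course clears.

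- Natural survival of carriage over an interval: s = exp(−28λ)
- Pooled survival: (1 − p)s + p·s(1 − e) = s(1 − pe)
- Implied rate: λ′ = λ − ln(1 − pe)/28

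With λ = 0.02 (mean 50 days) and e = 0.8:

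| p | 1 − pe | −ln(1 − pe)/28 | λ′ | Mean, days | Shorter by |
|---|---|---|---|---|---|
| 0.05 | 0.96 | 0.00146 | 0.02146 | 46.6 | 7% |
| 0.15 | 0.88 | 0.00457 | 0.02457 | 40.7 | 19% |
| 0.30 | 0.76 | 0.00980 | 0.02980 | 33.6 | 33% |

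For natural durations of 25 to 100 days, p from 0.05 to 0.30 and e from 0.5 to 0.8, the shortfall runs from 2% (24.4 against 25 days) to 49.5% (50.5 against 100 days). The formula gives courses to carriers at random and ignores reacquisition within an interval.

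**3. Burden with complete sampling and a perfect test.** A daily two-state chain was simulated for 365 days in 1000 infants per scenario, observed every 28 days. Half the infants were antibiotic users, with 7-day courses and daily clearance of 0.30 on treatment. A model without antibiotics was fitted, and daily status was reconstructed by forward-backward smoothing. Background acquisition and clearance were both 0.02 per day:

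| Courses per user per year | Fitted clearance | Users: true / estimated days | Non-users: true / estimated days |
|---|---|---|---|
| 2 | 0.022 | 155.0 / 156.9 (+1.2%) | 167.4 / 167.1 (−0.2%) |
| 4 | 0.024 | 137.6 / 140.2 (+1.9%) | 167.4 / 166.0 (−0.9%) |
| 8 | 0.027 | 113.1 / 117.2 (+3.7%) | 167.4 / 164.4 (−1.8%) |

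With no antibiotics at all, one half of the sample still showed an error of −2.4 days (172.6 against 175.0). The first two rows are therefore near simulation noise. With backgrounds of 0.01/0.01 and 0.02/0.05 per day as well, fitted clearance was 0% to 50% above the natural rate. The mean burden over all infants stayed within about 1.2 days of truth in every scenario. At 0.02/0.02, modelling antibiotics raised the correlation with true burden only from 0.943–0.945 to 0.948–0.951.

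**4. Burden with missing samples and an imperfect test.** The Discussion expects more missing data, and Objective 1 plans to estimate test sensitivity and specificity without a gold standard. The same design was run with 2000 infants, background 0.02/0.02, and test characteristics known to the model:

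| Assumption (8 courses per user) | Users: true / estimated | Non-users: true / estimated | Antibiotics modelled: users, non-users |
|---|---|---|---|
| 30% missing, sensitivity 0.90, specificity 0.97 | 113.0 / 124.5 (+10%) | 172.9 / 161.0 (−7%) | 112.5, 172.1 |
| 50% missing, sensitivity 0.85 | 113.6 / 131.5 (+16%) | 170.1 / 153.1 (−10%) | 114.2, 169.1 |

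With 30% missing and the imperfect test, the errors fall to about 2% to 3% at 2 courses per user and 3% to 5% at 4. A repeat of these runs gave results in line with these ranges.

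**The case against.** The strongest reply is that burden means days with the organism present, whatever ended the episode. Carriage ended by antibiotics is truly over, and the 4-weekly stools tie the reconstruction to observed status. This stands. A reader might infer that the Objective 3 burden is biased as a matter of course. The documents do not support that: mean burden is nearly right, and only the split between treated and untreated infants moves, usually by little.

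A reader might also infer that treated clearance is built into the design, because "All infants with acute disease (diarrhoea, fever) or severe acute malnutrition are linked with the nearby health facility". The text does not say that referred infants receive antibiotics. It also states that asymptomatic infection is not treated, and the Introduction describes colonisation as predominantly asymptomatic. Antibiotic treatment during follow-up is foreseeable, but its frequency is unknown.

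Further points have partial force:

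- The article never promises a natural clearance rate. The durations in step 2 of the working are shortfalls only against an antibiotic-free target.
- A condensed article may name covariates by category, and time since birth may track part of the change in feeding. Even so, the sentence is a stated specification, and these variables fall under none of its categories.
- Objective 3 adjusts for breastfeeding and infant health. That helps with confounding in the outcome model but does not correct the transition rates.
- The evidence on breastfeeding is cross-sectional, in children aged 10–16 months, from a study powered for prevalence. It justifies including the variable but does not show an effect on acquisition from birth.
- Animal-source food may lie on the path from livestock to infant. Adjusting acquisition for it could remove part of the effect of interest.

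**Conclusion.** The point holds in limited form. The stated transition model omits infant-level, time-varying information that the study already collects. Its clearance rate is a mixture and should not be reported as natural clearance. Its acquisition effects are not adjusted for breastfeeding.

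The effect on clearance ranges from negligible to large, depending on antibiotic frequency and effect, which the documents do not give. The effect on Objective 3 burden is a possible error of opposite sign in treated and untreated infants. It is at most about 4% with complete sampling, about 2% to 5% with moderate antibiotic use, 30% missing samples and an imperfect test, and about 7% to 16% with heavy use under the same or worse conditions. All these figures rest on assumed inputs. The change is worth making because it is cheap and because the Discussion concedes that only relatively strong associations can be detected.

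**What to change.** In Data analysis, Objective 1:

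- Add antibiotic use since the last stool as a time-varying regressor on clearance, and current breastfeeding as a time-varying regressor on acquisition.
- Report clearance for antibiotic-free intervals separately, and describe any overall rate as a mixture of treated and untreated clearance.
- Derive the Objective 3 burden from this version of the model.
- Examine animal-source-food intake in a secondary model only, because it may mediate the livestock effect.

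The cost is analysis wording and a few more coefficients; the data are already collected with each stool. Posteriors will be slightly wider. The antibiotic variable rests on maternal recall over about 4 weeks without exact course dates, so it cannot place clearance on a particular day. Its coefficient may also be confounded by indication, since the illness that prompts antibiotics may itself be linked to *Campylobacter*, and it should not be read as a treatment effect.
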